### Exploratory Outcomes

The schedule of enrollment, interventions, and assessments is summarized in Table 1 in accordance with the SPIRIT (Standard Protocol Items: Recommendations for Interventional Trials) guidelines [19]. The main exploratory cognitive outcome will be the change in MMSE score from baseline (visit 1) to 1 month after injury (visit 2). MMSE assessments will be conducted by 2 trained occupational therapists who are blinded to treatment allocation and are not involved in the intervention delivery. Secondary exploratory outcomes will include other cognitive assessments, including Montreal Cognitive Assessment, Verbal Fluency test, Boston Naming Test, Rey-Osterrieth Complex Figure Test, Rey Auditory Verbal Learning Test, Stroop test, Trail Making Test (parts A and B), Symbol Digit Modalities Test, and Digit Span Test [20,21]. Moreover, assessment of mental behavior will be assessed using the Neuropsychiatric Inventory, Pittsburgh Sleep Quality Index, Hamilton Anxiety Scale, Hamilton Depression Scale, Revised Apathy Rating Scale, and Cohen-Mansfield Agitation Inventory [22-26]. Neurological functions will be assessed by the Glasgow Coma Scale and modified Rankin Scale [27,28]. For assessment of activity of daily living and quality of life, the modified Barthel Index, Short Form 36 Health Survey, and Functional Activities Questionnaire will be evaluated. For neuroradiological assessment, functional connectivity within the default mode network and execution control network will be evaluated using MEG. Serum cognitive biomarkers including tau, amyloid beta, glial fibrillary acidic protein, S100 calcium-binding protein B, and alpha-synuclein will be tested.

**Table 1. T1:** Schedule of enrollment, interventions, and assessments.

Time points	Enrollment	Allocation (day 7)	1 month	3 months
Enrollment				
Eligibility screen	✓			
Informed consent		✓		
Randomization		✓		
Interventions				
MNS^a^		2 weeks  ^b^		
Sham MNS		2 weeks 		
Assessments				
Demographics, medical history	✓			
Laboratory data	✓		✓	✓
Neurological examination	✓		✓	✓
Neuroimaging (MRI^c^ and MEG^d^)		✓	✓	✓
Serum biomarkers		✓	✓	✓
Cognitive function		✓	✓	✓
Neuropsychiatric behavior		✓	✓	✓
ADL^e^ and quality of life		✓	✓	✓
Compliance			✓	✓
Drug combination	✓	✓	✓	✓
SAEs^f^ or AE^g^s			✓	✓

a MNS: median nerve stimulation.

b The intervention commenced 7 days after injury and was administered for 2 consecutive weeks.

c MRI: magnetic resonance imaging.

d MEG: magnetoencephalography.

e ADL: activities of daily living.

f SAE: serious adverse event.

g AE: adverse event.

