### Randomization

Once written informed consent has been obtained and eligibility has been confirmed, participants will be randomly assigned in a 1:1 ratio to either the active MNS group or the sham group. An independent investigator who is not involved in participant recruitment, intervention delivery, outcome assessment, or data analysis will generate the allocation sequence using an online computer-based randomization program. Randomization will be performed using a permuted block design with variable block sizes to ensure allocation concealment. No stratification factors will be applied. The allocation sequence will be securely maintained within the online randomization system and will remain inaccessible to the clinical investigators before randomization. After completion of the baseline assessment and confirmation of participant eligibility, the independent investigator will release the randomization code through the online system, and the participant will then be assigned to the corresponding treatment group. Clinical investigators cannot influence the randomization process.

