### Sample Size

This study is designed as a pilot RCT to evaluate the feasibility and safety of right MNS and to obtain preliminary estimates of treatment effects for planning a future definitive trial. Therefore, a formal sample size calculation based on statistical power for efficacy outcomes was not performed. A total sample size of 30 participants (15 per group) was considered appropriate for this pilot study. This sample size is consistent with recommendations for pilot randomized trials and is considered sufficient to estimate key feasibility parameters, including recruitment, adherence, retention, acceptability, and safety, as well as to provide preliminary estimates of treatment effect size and variability for planning a future definitive RCT [29]. In addition, the pilot study will be used to evaluate the predefined progression criteria and determine whether protocol modifications are required before proceeding to a larger trial.

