### Data Analysis

The feasibility outcomes will be reported using descriptive statistics. Recruitment, enrollment, adherence, and retention rates will be presented with 95% CIs. AEs and their frequency will also be summarized descriptively. Participant-reported symptom and acceptability questionnaire scores will be summarized using frequencies, percentages, medians, and IQRs, as appropriate. Baseline demographic and clinical characteristics will be summarized descriptively by the treatment group. No formal statistical significance testing will be performed for baseline characteristics. Exploratory cognitive outcomes will be analyzed according to the intention-to-treat principle where applicable. Missing outcome data will be handled using multiple imputation if appropriate. As this is a pilot feasibility trial with a small sample size, efficacy analyses are exploratory and are not powered to demonstrate definitive treatment effects. Group differences will be estimated using appropriate statistical methods according to the data distribution, with emphasis placed on effect sizes and 95% CIs rather than statistical significance. No formal adjustment for multiple comparisons will be performed. The estimated effect size for the MMSE will be used to inform the sample size calculation for the future definitive RCT.

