### Limitations

The present study has some potential limitations. First, the study aims to enroll patients with moderate TBI. Therefore, the findings should be interpreted with caution, particularly when generalizing to patients with mild or severe TBI. Second, because the sham intervention does not produce sensory and motor responses comparable to active MNS, participant blinding cannot be fully guaranteed, which may introduce expectancy effects and performance bias. This limitation should be considered when interpreting the study findings. Furthermore, results will only reflect short-term effects as the treatment duration will be only 2 weeks, and differences in patient lifestyles, treatment, and rehabilitation during the follow-up period may affect results. Therefore, we will collect relevant data during the follow-up period and adjust statistical analyses if needed.

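### The main MMSE comparison is a change score whose method is picked by data distribution; naming baseline MMSE as a covariate would tighten the estimate at almost no cost

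*Protocol article*

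**What the plan says.** Exploratory Outcomes in the Protocol article fixes the outcome: "The main exploratory cognitive outcome will be the change in MMSE score from baseline (visit 1) to 1 month after injury (visit 2"). Table 1 schedules cognitive testing at allocation (day 7), 1 month and 3 months, so a baseline MMSE is planned for every participant.

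Data Analysis gives the rule for estimation: "Group differences will be estimated using appropriate statistical methods according to the data distribution". It names no model and no covariate. The weight in reporting is on estimation: "with emphasis placed on effect sizes and 95% CIs rather than statistical significance". The section then gives the MMSE result a use: "The estimated effect size for the MMSE will be used to inform the sample size calculation for the future definitive RCT".

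Randomization says "No stratification factors will be applied". Sample Size says "A total sample size of 30 participants (15 per group) was considered appropriate for this pilot study", and that "a formal sample size calculation based on statistical power for efficacy outcomes was not performed".

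Adjustment is mentioned only in Limitations: "we will collect relevant data during the follow-up period and adjust statistical analyses if needed". In context this concerns lifestyle, treatment and rehabilitation differences arising after randomisation. It does not concern baseline MMSE.

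**The concern.** Choosing a method by how the data are distributed usually means choosing between a comparison of means and a rank method. Applied to change scores, either is most naturally carried out without baseline MMSE.

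Change is tied to the starting value here. Entry requires an MMSE of 26 or below. If the scale's maximum is taken as 30 (the article does not state it), a patient entering at 26 can gain at most 4 points, while one entering at 15 can gain 15. Patients selected for low scores also tend to drift upward on retest. A raw change carries this baseline-related variation into the comparison, and a model with baseline MMSE removes the linear part of it.

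What is at stake is the precision of the one efficacy estimate that the article carries forward to plan the next trial. There is a second cost. If skew leads the analyst to a rank method, the planned analysis may yield no mean difference and no SD to carry forward.

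**Working it through.** The plan has no efficacy figure to reproduce, since no effect size, SD, alpha or power is given. The check compares the 95% CI half-width of an unadjusted change score with that of a baseline-adjusted model.

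**Inputs.** From the article: n = 15 per arm, 95% CI. Assumed, because the documents do not give them: the correlation r between baseline and 1-month MMSE (varied), and equal SDs at the two visits, set to 1 so that results are in SD units.

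**Formulas.**
- Change score: t(28) × sqrt(2(1 − r) × 2/n)
- Baseline-adjusted: t(27) × sqrt((1 − r²) × (2/n) × (1 + 1/(2n − 4))). The last factor is 1 + 1/26 = 1.038, the price of estimating the baseline slope.

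Example at r = 0.5: change 2.048 × sqrt(1.0 × 0.1333) = 0.748; adjusted 2.052 × sqrt(0.75 × 0.1333 × 1.038) = 0.661. Then 1 − 0.661/0.748 = 11.6% narrower.

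| r | Change | Adjusted | Adjusted CI narrower by |
|---|---|---|---|
| 0.3 | 0.885 | 0.728 | 18% |
| 0.5 | 0.748 | 0.661 | 12% |
| 0.7 | 0.579 | 0.545 | 6% |
| 0.9 | 0.335 | 0.333 | about 0.5% |
| 0.95 | 0.237 | 0.238 | none |

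**Simulation check** (6,000 trials per setting). The ratio of change to adjusted half-width was 1.216, 1.131, 1.064 and 1.005 at r = 0.3, 0.5, 0.7 and 0.9 with 15 per arm. With 12 per arm (15 × 0.80, borrowing the 80% retention threshold as an assumed completion rate) it was 1.206, 1.125, 1.057 and 1.000.

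**Chance imbalance.** The SE of the baseline difference between arms is sqrt(2/15) = 0.365 SD. The chance of a difference beyond 0.5 SD in either direction is 17%. Given a 0.5 SD imbalance, the change-score estimate shifts by (r − 1) × 0.5, which is −0.35, −0.25 or −0.15 SD at r = 0.3, 0.5 or 0.7. In MMSE points, with an assumed SD of 5 and slope of 0.5, a one-SE imbalance is 0.365 × 5 = 1.83 points and moves the estimate by 1.83 × 0.5 = 0.91 points. Averaged over randomisations, both estimators were centred on zero in the simulation, where the true effect was zero.

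**Planning the definitive trial.** In large samples the variance of change relative to the adjusted residual variance is 2(1 − r)/(1 − r²) = 2/(1 + r), or 1.54, 1.33 and 1.18 at r = 0.3, 0.5 and 0.7. For the same difference in points, a trial sized on the change-score SD would need that many times the patients of one sized on the residual SD.

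**Equivalence.** Regressing change, or the 1-month score, on arm and baseline gave the same arm estimate in every simulated trial (differences below 1e-14).

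**The case against.** A reader might infer that the plan commits to an unadjusted analysis. It does not say so. The quoted sentence fixes the outcome, not the model, and a change outcome with baseline as a covariate gives the same arm estimate as the model recommended here. A statistical analysis plan that is not shown may already specify this, and a condensed article need not list covariates for an exploratory outcome. All of that stands, and it rules out calling the plan wrong. It does not remove the point. The article is not silent on method: it gives a selection rule, and a named baseline-adjusted model is better than that rule.

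A reader might also infer that baseline imbalance biases the estimate, or that the lack of stratification is an error. Neither is supported. The imbalance is sampling variation that the change-score CI already reflects, so the 0.91-point shift must not be counted in addition to the wider interval. Unstratified allocation is a reasonable choice for 30 patients at one centre.

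Finally, the percentages depend on an assumed r and on equal SDs, which the entry cut at 26 and a scale ceiling make doubtful. If the SDs differ, the size of the gain changes, although in large samples the adjusted estimate is never the less precise one.

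**Conclusion.** The point holds as an improvement to the stated rule, not as an error. The outcome is raw MMSE change, the method is left to the distribution of the data, and the only adjustment mentioned concerns follow-up differences. The most natural execution is therefore an unadjusted comparison of changes with 15 per arm. Against that, baseline adjustment would shorten the 95% CI by about 18%, 12% or 6% for an assumed r of 0.3, 0.5 or 0.7, and by essentially nothing from about 0.9 upward.

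Severity is low to moderate. The outcome is exploratory, and Progression Criteria rests the decision to proceed on feasibility and safety. The consequence is limited to a noisier MMSE estimate, and possibly a larger planning SD, passed to the definitive trial.

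**What to change.** In Data Analysis, replace selection of the method by distribution with a named model. The MMSE effect is the arm coefficient with its 95% CI from a linear model of 1-month MMSE (or, equivalently, change) on arm and baseline MMSE. Add a bootstrap CI as a check for skew or ceiling effects. Include arm and baseline MMSE in the multiple imputation model wherever imputation is used. Report the residual SD with the effect so that the definitive trial can be planned on it. If an unshown analysis plan already says this, aligning the article's wording with it is enough.

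The cost is a few sentences and one degree of freedom. No visit or measurement is added, and Results states that recruitment had not started at submission, so the change can be made before any data exist.

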### Sample Size

This study is designed as a pilot RCT to evaluate the feasibility and safety of right MNS and to obtain preliminary estimates of treatment effects for planning a future definitive trial. Therefore, a formal sample size calculation based on statistical power for efficacy outcomes was not performed. A total sample size of 30 participants (15 per group) was considered appropriate for this pilot study. This sample size is consistent with recommendations for pilot randomized trials and is considered sufficient to estimate key feasibility parameters, including recruitment, adherence, retention, acceptability, and safety, as well as to provide preliminary estimates of treatment effect size and variability for planning a future definitive RCT [29]. In addition, the pilot study will be used to evaluate the predefined progression criteria and determine whether protocol modifications are required before proceeding to a larger trial.

### Blinding

Investigators in charge of the recruitment and follow-up evaluation, outcome assessors, and data analysts will be blinded to group allocation. Participants and independent researchers who apply the MNS will not be blinded. Researchers who monitor patients’ safety and perform risk management can access group allocation if necessary. Before the outcome assessment begins at every follow-up evaluation, the participants will be reminded not to reveal any information about their group allocation to decrease the risk of unblinding. If the investigator can detect details of group allocation during follow-up, another blinded researcher will evaluate the outcome. To minimize performance bias, participants in both groups will receive identical standard care, follow the same treatment schedule and assessment procedures, and be managed according to the same clinical protocol throughout the study.

### Safety Monitoring

All AEs will be monitored throughout the study and recorded in the CRFs by the study investigators. Participants will be assessed for AEs during each intervention session and at every scheduled follow-up visit. The principal investigator will review all reported AEs and determine their severity, seriousness, and potential relationship to the intervention. Serious AEs will be reported promptly to the institutional ethics committee in accordance with institutional requirements. Participants will discontinue the intervention if they experience a serious device-related AE, meet any withdrawal criterion, or request withdrawal from the study.

An independent data monitoring committee (DMC) has been established to oversee participant safety, study conduct, and data integrity throughout the trial. The DMC will periodically review safety data and make recommendations regarding the continuation, modification, or termination of the trial if necessary. The study will also be conducted under the oversight of the institutional ethics committee, which will monitor compliance with the approved protocol and applicable ethical requirements.

### Data Analysis

The feasibility outcomes will be reported using descriptive statistics. Recruitment, enrollment, adherence, and retention rates will be presented with 95% CIs. AEs and their frequency will also be summarized descriptively. Participant-reported symptom and acceptability questionnaire scores will be summarized using frequencies, percentages, medians, and IQRs, as appropriate. Baseline demographic and clinical characteristics will be summarized descriptively by the treatment group. No formal statistical significance testing will be performed for baseline characteristics. Exploratory cognitive outcomes will be analyzed according to the intention-to-treat principle where applicable. Missing outcome data will be handled using multiple imputation if appropriate. As this is a pilot feasibility trial with a small sample size, efficacy analyses are exploratory and are not powered to demonstrate definitive treatment effects. Group differences will be estimated using appropriate statistical methods according to the data distribution, with emphasis placed on effect sizes and 95% CIs rather than statistical significance. No formal adjustment for multiple comparisons will be performed. The estimated effect size for the MMSE will be used to inform the sample size calculation for the future definitive RCT.

### Progression Criteria

The primary purpose of this pilot study is to determine whether a future definitive RCT is feasible. Progression to a full-scale RCT will be guided by predefined feasibility and safety criteria rather than exploratory efficacy outcomes. Specifically, progression will be considered feasible if the following criteria are met: (1) an enrollment rate of at least 60% among eligible patients; (2) a recruitment rate of at least 2 participants per month; (3) an adherence rate of at least 80% of the prescribed stimulation sessions; (4) a retention rate of at least 80% at the 3-month follow-up; (5) no unexpected serious device-related AEs attributable to the intervention; and (6) acceptable participant satisfaction with the intervention, defined as a median score of ≥4 on the 5-point Likert acceptability questionnaire. If one or more of these criteria are not achieved, the feasibility findings will be carefully reviewed to identify barriers and determine whether modifications to the study design, intervention protocol, recruitment strategy, or outcome assessments are required before proceeding to a future definitive RCT. Exploratory efficacy outcomes will be used to estimate treatment effects and variability to inform the sample size calculation and design of the subsequent trial, but they will not determine progression to the definitive study.

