### Interventions

Participants will receive right MNS (active or sham) for 2 consecutive weeks in addition to standard care. During the intervention period, medications that may affect cognitive function will not be permitted. The median nerve stimulator (XCH-B1; Jiangxi Nuocheng Electric Co Ltd) delivers asymmetric biphasic pulses. In the active MNS group, stimulation will be delivered at a fixed frequency of 40 Hz with a pulse width of 300 µs using a 20-second ON or 40-second OFF duty cycle. During the first treatment session, the treating investigator will set the stimulation intensity between 15 and 20 mA according to individual tolerance. The intensity may subsequently be adjusted within this range if necessary to maintain a visible thumb flexion while remaining comfortable and well tolerated by the participant. Participants in the sham group will use an identical device with the same electrode placement, treatment duration, and operating procedures as those in the active MNS group. However, the device will be programmed to deliver 0 mA, thereby providing no electrical stimulation. This sham procedure was selected to control for the nonspecific effects associated with device application while avoiding unintended activation of the median nerve. Participants will be instructed not to modify the stimulation parameters independently. Any adjustment to the stimulation intensity will be performed only by the study investigator when clinically indicated.

Two self-adhesive surface electrodes will be placed over the right median nerve on the volar aspect of the forearm. The distal electrode (anode, +) will be positioned approximately 2 fingerbreadths proximal to the wrist crease, and the proximal electrode (cathode, −) will be positioned approximately 2 fingerbreadths proximal to the distal electrode along the course of the median nerve. Before the first treatment session, study personnel will verify correct electrode placement and provide standardized instructions regarding the intervention procedure. The stimulation site will be inspected before each treatment session for erythema, irritation, blistering, or other signs of skin injury.

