### Outcomes

#### Primary Outcome

##### Feasibility

Referring to the previous recommendations, the feasibility of this pilot study will be evaluated based on the following measures: (1) enrollment rate—the proportion of participants who meet the eligibility criteria and provide consent after baseline screening; (2) recruitment rate—the mean number of participants enrolled in the study per month; (3) adherence rate—the proportion of completed scheduled stimulation hours, which will be used to assess the acceptability of the interventions; and (4) retention rate—the proportion of participants who complete all outcome measurements from the baseline to follow-up assessments [15,18]. These measures will determine whether to proceed with a future main trial.

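### The adherence and acceptability progression criteria name no arm, so read as written they mix 0 mA sham data into the test of whether active MNS is tolerated and accepted

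*Protocol article*

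**What the plan says.** All references are to the Protocol article.

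- **Progression Criteria.** Criterion 3 is "an adherence rate of at least 80% of the prescribed stimulation sessions". Criterion 6 is satisfaction with the intervention, "defined as a median score of ≥4 on the 5-point Likert acceptability questionnaire". The criteria are described as predefined, and neither names an arm. A missed criterion leads to a review and possible changes to the design.
- **Outcomes, Feasibility.** Adherence is "the proportion of completed scheduled stimulation hours, which will be used to assess the acceptability of the interventions". The last word is plural and no arm is named.
- **Interventions.** "Participants will receive right MNS (active or sham) for 2 consecutive weeks in addition to standard care". Sham participants have the same treatment duration and procedures, but "the device will be programmed to deliver 0 mA, thereby providing no electrical stimulation".
- **Safety Evaluation.** The 10-item questionnaire goes to participants, without restriction to the active arm.
- **Sample Size.** "A total sample size of 30 participants (15 per group) was considered appropriate for this pilot study", and that total is presented as enough to estimate adherence and acceptability, among other things.
- **Data Analysis.** "Recruitment, enrollment, adherence, and retention rates will be presented with 95% CIs". Only baseline characteristics are said to be summarised by treatment group.
- **Blinding.** Participants are not blinded.

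**The concern.** The pilot asks whether patients with acute TBI can complete, and will accept, median nerve stimulation for 8 hours a day over 2 weeks, at 15 to 20 mA with visible thumb movement. Criteria 3 and 6 are the progression criteria that address this. A sham participant feels no current and has no thumb flexion. The Limitations section itself says that the sham does not reproduce the sensory and motor responses. Sham data show the burden of wearing a device and keeping a schedule. They do not show tolerance of stimulation.

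If half of each figure comes from sham participants, the rule can report success when the active arm is below the threshold. That is the more harmful error: a missed criterion at least prompts a review, whereas a pooled pass prompts none.

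The other criteria do not cover the gap. Criterion 5 concerns only serious device-related events that were not expected, so ordinary discomfort or refusal does not trigger it. The retention criterion also names no arm.

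**Working it through.** The 80% and ≥4 thresholds are set, not derived, so there is no plan calculation to reproduce. The sample size agrees: 15 + 15 = 30.

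**Adherence**

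Inputs: 8 hours a day for 14 days (Interventions) and 15 participants per arm (Sample Size).

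- Scheduled hours per participant: 8 × 14 = 112.
- Per arm: 15 × 112 = 1,680. Both arms: 3,360.
- Pooled threshold: 0.80 × 3,360 = 2,688 hours.
- With equal arms, pooled adherence = (active + sham)/2, so at the threshold active = 1.60 − sham.

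| Sham adherence | Active adherence that still gives 80% pooled |
|---|---|
| 100% | 60% (1,008 of 1,680 h) |
| 95% | 65% |
| 90% | 70% |

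Judged in the active arm alone, the same threshold needs 0.80 × 1,680 = 1,344 hours.

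The Feasibility section counts hours and the Progression Criteria count sessions. The formula is the same for either unit as long as the arms have equal schedules.

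**Acceptability**

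Assumption: each participant has one score from 1 to 5. The article does not show how the 10 items become one score, so these cases are illustrations. With 30 responses the median is the mean of the 15th and 16th ordered scores. In the active arm alone it is the 8th of 15.

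| Sham scores | Active scores | Pooled median | Active median |
|---|---|---|---|
| 15 × 5 | 15 × 3 | (3+5)/2 = 4.0, pass | 3 |
| 15 × 4 | 14 × 1, one 4 | (4+4)/2 = 4.0, pass | 1 |
| 15 × 5 | 15 × 1 | (1+5)/2 = 3.0, fail | 1 |
| 14 × 5, one 4 | 15 × 3 | (3+4)/2 = 3.5, fail | 3 |
| 15 × 3 | 15 × 4 | (3+4)/2 = 3.5, fail | 4 |

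The third row shows that sham scores alone are not enough when all 30 respond. If one active questionnaire is missing, the median is the 15th of 29 scores, and 15 sham scores of 4 or more are then enough on their own. The fourth row shows that the first is a borderline case. The last row shows the opposite error: the active arm meets the threshold and the pooled figure fails.

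**How likely this is, under assumed rates**

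Suppose each active participant scores 4 or more with probability 0.30, and take a pooled pass as at least 16 of 30 scoring 4 or more. This is slightly strict, because a 3 and a 5 in the middle would also average 4.

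| Assumed sham probability of scoring ≥4 | Pooled pass | Active-only pass (≥8 of 15) |
|---|---|---|
| 0.50 | 9% | 5% |
| 0.70 | 42% | 5% |
| 0.80 | 67% | 5% |
| 0.90 | 88% | 5% |

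The reverse case follows by symmetry. With active 0.70 and sham 0.30, the pooled pass probability is again 42%, while the active-only figure is 1 − 0.05 = 95%. The documents give none of these rates. They show only how strongly the pooled result depends on the sham arm.

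**Retention, as a check on the other criteria**

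24 of 30 retained is 80% and passes. If all six losses are in the active arm, active retention is 9/15 = 60%.

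**The case against.** The strongest reply is that pooling is inferred. No sentence says that the arms are combined. The article is a condensed text, and by-arm tables may stand in the full protocol or the analysis plan. The stated objective is the feasibility of MNS, the Abstract contrasts a stimulation group with a sham group, and the intervention in criterion 6 could mean active treatment only. This stands in part: pooling is the natural reading but not an explicit one. However, the protocol calls both arms' treatment MNS and the Abstract describes the sham group as receiving stimulation, so the vocabulary does not settle the matter. By-arm tables elsewhere would not say which number is compared with 80% or with 4.

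Second, a reader might infer that 15 sham participants can carry the trial past both criteria by themselves. The documents do not support that for criterion 6: with all 30 responding, at least one active score of 3 or more is needed. Nor is the direction certain. The questionnaire also covers perceived benefit and willingness to repeat treatment, and participants who know that they receive 0 mA may score these low.

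Third, sham data are relevant. A definitive sham-controlled trial also needs control participants who wear the device and stay in the study, and several listed reasons for lost time can affect either arm. This stands, and it argues against discarding the sham figures.

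Fourth, daily duration, interruptions and adverse events are recorded, so poor active tolerance would be visible to anyone who looks. This lowers the severity but does not repair the rule.

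**Conclusion.** The point holds at moderate severity. As worded, criteria 3 and 6 take in sham participants and so do not measure tolerance or acceptability of active MNS. An active arm up to 20 percentage points below the adherence threshold can pass (60% with full sham adherence), and an active median below 4 can pass criterion 6. A false failure of criterion 6 is also possible.

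This rests on the pooled reading, on equal arms of 15, and for criterion 6 on one score per participant and on assumed sham scores. A reader might conclude that a definitive trial would start automatically with an intolerable intervention. The text does not support that: the criteria guide progression, a miss leads to review, and the Discussion allows for redesign.

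**What to change.** In the Progression Criteria, state that criteria 3 and 6 must be met in the active MNS arm, with thresholds unchanged. Report sham-arm adherence and acceptability separately, as evidence on the burden of wearing the device and on the feasibility of the control arm. Requiring adherence to be met in each arm is a reasonable alternative that covers both risks. Use one unit for adherence, hours or sessions, in the Feasibility section and in criterion 3.

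In Data Analysis, state that adherence, retention and questionnaire results are presented by arm.

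The cost is wording and precision. The data are already to be collected, and recruitment had not begun at submission. Each arm's estimate rests on 15 participants. For a participant-level rate of 80%, the exact 95% CI is 61% to 92% for 24/30 and 52% to 96% for 12/15. The wider interval reflects how much the pilot can tell about active MNS.
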